### Sample Size

We will aim to enroll 48 participants. The sample size for this study was determined by detecting a clinically meaningful increase in anaerobic threshold (AT) in patients awaiting MBS. Previous research in a comparable patient cohort [37] reported a mean AT of 11.0 (SD 1.5) mL/kg/min among 95 patients. In this study, we aim to detect a 150 mL O_2_ increase in AT, corresponding to a mean difference of 1.15 mL/kg/min between the two groups. This threshold was selected based on literature indicating that changes of approximately 0.75-1.25 SDs in AT are associated with improved perioperative risk profiles and functional capacity in surgical populations [37-39]. We calculated that a sample size of 21 participants per group would be sufficient to detect a 150 mL O_2_ increase in AT, with a significance level of .05 and a power of 0.80. This calculation is based on having 2 repeated measurements per participant and an intracluster correlation of 0.5. Pilot research by Gilbertson et al [40] has informed our anticipated dropout rate of less than 10%, or 2 participants per treatment arm.

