#### Statistical Analysis Plan

Descriptive statistics will be used to summarize baseline characteristics and the primary outcome by treatment group, using mean (SD) and median (IQR) for continuous data and frequency (%) for categorical data. The distribution of the primary outcome will also be graphically investigated.

Treatment effect will be presented as the estimate and a 95% CI. This will be estimated from a linear mixed regression model with repeated measures of the outcomes at baseline and 4 weeks, with a random intercept for participants to account for correlations between repeated measures over time within participants. The model will include, as fixed effect a treatment arm indicator (during the follow-up phase only) and a time indicator (baseline or follow-up). All analyses will be performed on an intention-to-treat basis, and all modelling assumptions will be checked (eg, residuals).

A complier average causal effect estimate will be calculated to investigate potential effect of non-compliance. The number (%) of participants with missing outcomes will be summarized by treatment arm. A sensitivity analysis that includes predictors of missingness as covariates in the primary analysis model will be conducted. Multiple imputation will also be performed as an additional sensitivity analysis for missing data. A per-protocol analysis will also be carried out as a sensitivity analysis. The effect of the intervention on secondary outcomes will be assessed using methods analogous to those used for the primary outcome.

Satisfaction survey responses from the intervention group will be summarized descriptively. Where appropriate, exploratory analyses will examine variation in responses based on participant characteristics (eg, age, baseline fitness, engagement in sessions) to identify factors associated with higher acceptability or satisfaction.

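### Adding predictors of missingness as plain covariates to the two-visit model corrects only part of any predictor-driven loss to visit 2; a predictor-by-time term would complete the correction

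*Protocol article*

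**What the plan says.** The Statistical Analysis Plan section of the protocol article estimates the treatment effect from a "linear mixed regression model with repeated measures of the outcomes at baseline and 4 weeks, with a random intercept for participants". The fixed effects are "a treatment arm indicator (during the follow-up phase only) and a time indicator (baseline or follow-up"). Baseline is thus an outcome row, and the arms share a common baseline mean.

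Two analyses deal with missing outcomes. One is described as follows: "A sensitivity analysis that includes predictors of missingness as covariates in the primary analysis model will be conducted". The other is: "Multiple imputation will also be performed as an additional sensitivity analysis for missing data". The article names no predictors. It neither mentions nor rules out a predictor-by-time term, and it does not state the imputation model.

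The Sample Size section expects dropout below 10%, or 2 participants per arm.

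**The concern.** In an analysis of covariance with the 4-week value as the only outcome, an added covariate adjusts that value directly. Here the same step does something different. With both visits as outcome rows, a covariate without a time interaction moves a participant's overall level by the same amount at both visits.

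The model already uses baseline anaerobic threshold (AT). A further predictor helps only through what it says about the 4-week value beyond baseline, and a shared slope captures that poorly. The section writes the arm term explicitly as acting at follow-up only, but gives the predictors no such term.

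What is at stake is how a sensitivity analysis is interpreted. If its estimate stays close to the primary one, that will be read as robustness. It may instead mean that the covariate form could not remove the bias, even where a measured variable fully explains the loss.

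**Working it through.** **Inputs from the protocol (Sample Size).** The cited cohort "reported a mean AT of 11.0 (SD 1.5) mL/kg/min among 95 patients"; the target is an increase "corresponding to a mean difference of 1.15 mL/kg/min between the two groups"; the calculation is made "with a significance level of .05 and a power of 0.80"; there are two measurements with intracluster correlation 0.5. Two-sided testing is assumed.

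**The plan's own figure.** n per arm = 2(1 − ρ²)[SD(z₀.₉₇₅ + z₀.₈₀)/δ]² = 2(0.75)[1.5 × 2.8016/1.15]² = 20.03, rounded up to 21, which is the stated number. The SD and correlation are therefore the right ones to carry forward.

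**Assumptions not in the protocol.** X is a standardized predictor with slope b₀ on baseline AT and b₁ on 4-week AT, in mL/kg/min per SD. Exercise participants with the lowest X miss visit 2, and control loss is random. Planned loss is 2/24 = 8.3%; 3/24 = 12.5% is also shown.

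**Large-sample algebra.** With equal variances, the model's arm effect is the between-arm difference in Y₁ − ρY₀ among those seen at visit 2. Let m be the between-arm difference in mean X among them.

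- No predictor: bias = (b₁ − ρb₀)m.
- Predictor with one shared slope g: bias = [b₁ − ρb₀ − (1 − ρ)g]m. With few values missing, g ≈ (b₀ + b₁)/2.
- Predictor plus predictor-by-time: both slopes are free, so bias = 0.
- Share left with the shared slope = 1 − (1 − ρ)g/(b₁ − ρb₀).

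Share left at ρ = 0.5:

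- Equal slopes (0.5, 0.5): 1 − 0.5(0.5)/0.25 = 0%.
- Slopes 0.25 and 0.5: 1 − 0.5(0.375)/0.375 = 50%.
- Slopes 0 and 0.5: 1 − 0.5(0.25)/0.5 = 75%. Missing 4-week values pull g toward b₀, so the simulated share is somewhat higher.

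For loss of the lowest fraction p, m = φ(z_p)/(1 − p), which is 0.167 at 2/24 and 0.235 at 3/24. As an example, slopes 0 and 0.5 at 3/24 with no predictor give 0.5 × 0.235 = 0.118.

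**Simulation check.** Generalized least squares with ρ = 0.5 on 2,000,000 simulated participants, true effect 1.15. Entries are bias in mL/kg/min; simulation error is a few thousandths.

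| Lost | b₀, b₁ | No predictor | Shared slope | With time interaction | Share left |
|---|---|---|---|---|---|
| 2/24 | 0.5, 0.5 | +0.041 | 0.00 | 0.00 | about 0% |
| 2/24 | 0.25, 0.5 | +0.060 | +0.031 | 0.00 | 51% |
| 2/24 | 0, 0.5 | +0.087 | +0.069 | 0.00 | 80% |
| 2/24 | 0, 0.75 | +0.125 | +0.099 | 0.00 | 79% |
| 3/24 | 0.5, 0.5 | +0.061 | 0.00 | 0.00 | about 0% |
| 3/24 | 0.25, 0.5 | +0.091 | +0.050 | 0.00 | 55% |
| 3/24 | 0, 0.5 | +0.118 | +0.094 | 0.00 | 80% |
| 3/24 | 0, 0.75 | +0.176 | +0.141 | 0.00 | 80% |

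**Sensitivity to the assumptions.** A second setup had about 10% missing in each arm, with X driving loss in opposite directions by arm.

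- Predictor unrelated to baseline, residual correlation 0.5: 79% left at a 4-week slope of 0.25, falling to 65% at 1.5.
- 4-week slope 0.5, no baseline slope: 68% left at ρ = 0.3, 85% at 0.7 and 94% at 0.9.
- Slopes of opposite sign (−0.25, 0.5): 92% left.
- When X drives loss equally in both arms and does not modify the effect, the primary model has essentially no bias to remove.

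**Multiple imputation.** In that setup with slopes 0 and 0.5, imputing by arm from baseline AT and X left a bias of +0.002. The primary model had −0.090 and the shared-slope analysis −0.068.

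**The case against.** The strongest reply is that this is one sentence in a journal article. It does not forbid a time interaction, and the full analysis plan may contain one. That stands in part: the point concerns the ordinary reading of the sentence, under which a covariate is a main effect, and it disappears if the full plan already has the interaction.

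A reader might infer that the analysis leaves about 80% of the bias whatever the predictor, and that it will give false reassurance. The documents support neither. The 80% belongs to a predictor unrelated to baseline AT with correlation near 0.5. Stable characteristics such as age or BMI may relate to AT at both visits, which is the low end of the range. False reassurance would also require the multiple imputation to miss the problem, and that has not been shown.

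A reader might also infer that session attendance, as a predictor of missingness, would wipe out the treatment effect. The protocol never proposes attendance as a covariate, and handles non-compliance through separate complier-average and per-protocol analyses. The arm effect falls to about 0 only if attendance is entered with a time interaction or as a time-varying covariate; as a constant main effect it moved the estimate only from 1.15 to 1.13. The attendance point is therefore a guard to accompany the fix, not a fault in the plan.

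Finally, the loss pattern used here is deliberately strong and differs by arm. The standard error at 21 per arm is 1.5 × √0.75 × √(2/21) = 0.40, so a residual bias of 0.14 is about 0.35 of a standard error.

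**Conclusion.** The point holds in a limited form. Read as main effects, the planned covariates cannot fully correct loss to visit 2 that relates to the 4-week value or the change and differs by arm. A predictor-by-time term can, provided the predictor does not modify the treatment effect.

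The share of bias left is about 0% to 80% or more, depending on how the predictor relates to the two visits. Near the planned dropout this is about 0 to 0.14 mL/kg/min, or at most about 12% of the 1.15 target (0.14/1.15). These sizes rest on assumed predictor strengths and an assumed loss pattern, neither of which the protocol gives.

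The primary analysis is not affected. Severity is minor: a cheap improvement to one of two missing-data checks.

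**What to change.** Replace the sentence with wording such as:

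> A sensitivity analysis will add baseline predictors of missingness, each with its interaction with time, to the primary model; the same predictors will be included in the multiple imputation model, and post-randomization variables will not be entered as covariates.

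The last clause is needed because the interaction would otherwise let variables such as attendance absorb part of the treatment effect.

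The cost is one extra parameter per predictor, in a sensitivity analysis only. With 48 participants that is a reason to keep the list of predictors short. The change does not cover predictors that modify the treatment effect: in a scenario where X acted only through effect modification, bias was −0.095 without the predictor and −0.094 with the interaction. Enrollment was still ongoing when the article was written, so the wording could be settled before outcome data are examined.

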#### Monitoring

The chief investigator will be responsible for the day-to-day monitoring and management of the study. The UCLH/UCL Joint Research Office, on behalf of UCL as Sponsor, will monitor and conduct random audits on a selection of studies in its clinical research portfolio. Monitoring and auditing will be conducted in accordance with the Department of Health Research Governance Framework for Health & Social Care [54] and in accordance with the sponsor’s monitoring and audit policies and procedures.

#### Data Monitoring

In accordance with the UCL Records Retention Policy, at the end of the trial, all essential documentation will be archived securely by the chief investigator for a minimum of 20 years from the declaration of the end of trial. After 20 years, stored data will be securely destroyed.

#### Harms

In alignment with SPIRIT guidelines [35], adverse event monitoring and handling procedures have been established to ensure participant safety. Given the telehealth nature of the intervention, specific adaptations have been made to address challenges related to remote supervision, participant adherence, and emergency response. Participants are required to complete thorough pre-exercise screening, and real-time monitoring is conducted through online sessions by the supervising exercise physiologist. Additionally, clear protocols are in place for identifying and responding to adverse events, including escalation procedures for medical concerns and access to emergency services if needed. For research staff, there is a potential risk of sustaining an injury when assisting patients on and off the exercise equipment; however, this is part of the routine procedure in exercise testing, and only experienced staff will undertake this role. Manual handling and intermediate life support training have been completed by all involved staff.

#### Research Events and Incidents

In this trial, adverse events have been defined as any untoward medical occurrence in a trial participant, which does not necessarily have a causal relationship with the intervention. Serious adverse events are defined as any adverse event that results in death, is life-threatening (an event in which the participant was at risk of death at the time of the event; it does not refer to an event that hypothetically might have caused death if it were more severe), requires hospitalization (inpatient admission), or results in persistent or significant disability or incapacity.

The number, nature, and severity of serious adverse events (if any) will be reported separately by study arm at each follow-up time point. The number of participants who experience adverse events will likewise be reported separately by study arm.

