### Eligibility Criteria

Participants will consist of adults aged ≥18 years who are enrolled in the bariatric surgery programs at selected sites, with BMI ≥30 kg/m^2^. Patients must have ≤5% variation in body weight over the preceding 3 months, be willing and able to comply with the trial protocol, and provide written informed consent.

A patient who meets any of the following criteria will be excluded from participation in this study: currently pregnant or lactating, body mass ≥180 kg (due to weight restrictions of equipment), currently using beta-blockers, participating in another clinical intervention trial, clinically significant medical comorbidities present (eg, uncontrolled hypertension, unstable cardiovascular disease) that could increase the risk of an adverse response to exercise [36], or a history of atrial fibrillation, unstable angina, acute coronary syndrome, or congestive heart failure (New York Heart Association class III–IV) within the preceding 12 months.

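### The serious adverse event definition has no category for other medically important events, so an emergency call-out that meets none of its four criteria is non-serious and reaches only a participant count

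*Protocol article*

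**What the plan says.** The Research Events and Incidents section of the protocol article sets the rule: "Serious adverse events are defined as any adverse event that results in death, is life-threatening". A parenthesis limits the life-threatening criterion to "an event in which the participant was at risk of death at the time of the event" and expressly shuts out events that could only have been fatal in a worse form. The list then closes with an event that "requires hospitalization (inpatient admission), or results in persistent or significant disability or incapacity". No further category follows.

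The same section sets two reporting levels. For serious events: "The number, nature, and severity of serious adverse events (if any) will be reported separately by study arm at each follow-up time point". For adverse events in general: "The number of participants who experience adverse events will likewise be reported separately by study arm".

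The Harms section describes the response to adverse events as "including escalation procedures for medical concerns and access to emergency services if needed". Eligibility Criteria excludes people with, in the preceding 12 months, "a history of atrial fibrillation, unstable angina, acute coronary syndrome, or congestive heart failure", which shows the kind of event the trial regards as a hazard of exercise.

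**The concern.** The two criteria most likely to catch an acute event during exercise are both narrowed in the text: life-threatening to actual risk of death, and hospitalization to inpatient admission. Nothing covers what falls between them. Yet the article itself provides for calling emergency services, and such a call need not end in admission.

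What is at stake is how safety is reported. Adverse events are defined very broadly, as any untoward occurrence whatever its cause. An emergency call-out classed as non-serious would therefore stand in the same count as muscle soreness. The trial could truthfully report no serious adverse events although emergency services had been called to a session. The Conclusions of the Abstract expect the results to guide practice and policy, so readers would need to see such events described.

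**Working it through.** The article gives no figure to reproduce, because the point turns on wording. The check sets the criteria against an event that the plan itself foresees.

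**Step 1. Exposure to exercise (Interventions; Outcomes; Sample Size).**
- Every participant has a maximal cardiopulmonary exercise test at visit 1 and again at visit 2. If all 48 complete both, that is 48 × 2 = 96 tests.
- The intervention arm (48 / 2 = 24 participants) has 7 remote supervised sessions each: 24 × 7 = 168 sessions at moderate to vigorous intensity. Self-led activity is encouraged on top.

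**Step 2. An illustrative event against each criterion.** Take exercise syncope or a new arrhythmia. Emergency services are called, the participant is treated in an emergency department and goes home the same day.

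| Criterion | Met? |
|---|---|
| Death | No |
| Life-threatening | Only if there was actual risk of death at the time |
| Inpatient admission | No |
| Lasting or significant disability | Only if the event leaves it |

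Where neither conditional answer is yes, the event meets no criterion and is non-serious. The investigator has no clause under which to judge otherwise.

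**Step 3. What is then reported.** For a serious event, the section promises number, nature and severity by arm. For a non-serious one, it promises the number of participants affected by arm. Nature and severity are named only at the first level.

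**Step 4. Attribution to an arm.** Under Allocation, randomization follows baseline data collection. Of the 96 planned tests, 48 therefore take place before anyone has been allocated. An event at a baseline test cannot be an effect of either arm and would blur a by-arm table if it were counted there.

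**The case against.** The strongest objection is that this is a condensed article. The Harms section says that procedures for identifying and responding to adverse events exist, and seriousness assessment and event narratives commonly sit in a full protocol or on a reporting form that is not shown. The sections cited are also compatible with one another, so nothing here is a contradiction. This stands in part. The full protocol may hold a wider list. But the article does not leave the definition to another document: it states it in full, with two limiting parentheses. If the full protocol is wider, the published definition misstates it and still needs correcting.

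Three stronger readings are tempting, and the documents do not support them.
- A reader might infer that every cardiac event without admission is non-serious. It is not. Death, actual risk of death and lasting disability are separate criteria that need no admission.
- A reader might infer that such events would go unrecorded or unmanaged. The article does not say so. The response and escalation procedures apply to adverse events generally, and silence on nature and severity is no statement that they will be withheld. What the text shows is a gap in classification and in the promised reporting.
- A reader might object that prolonged hospitalization is missing too. It matters little here: participants are outpatients awaiting surgery, any inpatient admission for an adverse event already qualifies, and Strengths and Limitations states that there is no postoperative follow-up.

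**Conclusion.** The point holds in a limited form. The definition is a closed list of four criteria without a category for other medically important events. An event that triggers emergency escalation but meets none of the four is non-serious, and the only output stated for it is a count of participants.

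The size cannot be put as a rate. The documents give no incidence of such events and no share that would end without admission, so any percentage would be invented. With 48 participants planned, a handful of events, or a single one, could decide what the trial says about safety. No outcome, effect estimate or sample size figure is affected.

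The conclusion assumes that the definition is applied as published and that the unshown procedures do not widen it.

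**What to change.** 1. Add a fifth criterion to the list in Research Events and Incidents: *or is otherwise judged medically important by the investigator*.
2. State that any event in a remote session or an exercise test that triggers emergency escalation is assessed against this criterion.
3. Report the nature and severity of these events by arm, whatever the result of that assessment. List events at the baseline test separately, because they precede randomization.

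If the full protocol already contains such a criterion, it is enough to bring the published definition into line and to state the reporting rule.

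The cost is small but not nil. The count of serious events may come out slightly higher. By May 2025, 30 of the 48 planned participants had enrolled, so events already recorded must be reassessed under the new criterion. Otherwise, earlier and later participants would be classified by different rules. No new data collection is needed if adverse events have been recorded as the article defines them. The reassessment can be completed before results are submitted, which the article expects by mid-2026.

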### Interventions (Preoperative Exercise Group Only)

A 4-week structured exercise program will be delivered online using a cloud-based video conferencing service [42]. Participants in the exercise intervention group will individually undertake 7 instructor-led exercise sessions across the 4-week intervention period. In addition, participants will be provided with existing digital guidelines for presurgery exercise [43] and encouraged to participate in self-led PA on as many days as possible during the 4-week period. To guide this, participants will have access to prerecorded online exercises and are encouraged to replicate supervised sessions during each self-led session. The program is designed to meet the National Physical Activity Guidelines [44] of at least 150 minutes of low-to moderate-intensity or 75 minutes of vigorous PA per week, or a combination of the two [45]. Participants will be asked to record daily PA in an electronic diary, alongside a standardized exercise-related rating of perceived exertion [46] for each session and duration of exercise participation.

Sessions will be supervised by an accredited exercise physiologist, who is a university-qualified allied health professional with training in the design and delivery of safe and effective exercise interventions for people with chronic medical conditions, injuries, or disabilities [47]. Participants are offered a range of scheduling options to accommodate varying availability, including morning and afternoon time slots on both weekdays and weekends, with options within and outside standard business hours. If an appointment is canceled or missed, our protocol permits rescheduling within a 5-day window to maintain consistency with study timelines.

Each supervised session (Table 1) will consist of aerobic and resistance exercises, targeting all main muscle groups and tailored to participants based on their exercise history and limitations. Participants’ baseline functional level will guide the targeted exercise prescription. Sessions will be prescribed at moderate- to vigorous-intensity (Table 2) for a 30-minute duration. A set of varying-resistance exercise bands will be provided for participants.

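### Nature and severity are planned for serious adverse events only, so non-serious exercise-type harms would not be distinguishable from unrelated illness in the planned report

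*Protocol article*

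**What the plan says.** All the relevant text is in the protocol article, under Research Events and Incidents unless another section is named.

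- **Definition.** "adverse events have been defined as any untoward medical occurrence in a trial participant, which does not necessarily have a causal relationship with the intervention". The definition is all-cause and applies to both arms.
- **Seriousness.** An event is serious if it is fatal or life-threatening, "requires hospitalization (inpatient admission), or results in persistent or significant disability or incapacity".
- **Reporting of serious events.** "The number, nature, and severity of serious adverse events (if any) will be reported separately by study arm at each follow-up time point".
- **Reporting of adverse events overall.** "The number of participants who experience adverse events will likewise be reported separately by study arm".
- **Handling.** The Harms section covers pre-exercise screening, live observation by the exercise physiologist and escalation; it states that "clear protocols are in place for identifying and responding to adverse events, including escalation procedures for medical concerns". It does not say what will be reported. The only injury it names is one that research staff might sustain when helping patients on and off equipment.
- **Exposure.** Exercise-arm participants "will individually undertake 7 instructor-led exercise sessions across the 4-week intervention period", and are encouraged to add self-led activity on as many days as they can (Interventions). Both arms have cardiopulmonary exercise testing (CPET) at visits 1 and 2 (Outcomes).
- **Outcomes.** The secondary outcomes named in the Abstract and the assessments listed under Outcomes include no measure of harm. The full outcome list is in an appendix that is not shown.

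**The concern.** The two reporting sentences stand next to each other and set different levels of detail. The word linking the second to the first carries over the split by arm. It does not carry over nature or severity, because the second sentence names its own, narrower quantity: participants with an event.

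The narrower level applies where this trial's harms are most likely to fall. The programme includes lunges, balance work and band exercises, is aimed at an exertion described as hard (Table 1), and is done at home by people with a BMI of at least 30 kg/m². A strain, a fall without admission, a sore joint or a dizzy spell is an adverse event but would not normally meet a seriousness criterion. Under the stated plan it adds at most one person to a total that also contains colds and headaches. If that person already had another event, it adds nothing.

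The article says the trial will help determine whether the programme suits the preoperative pathway (Abstract) and will guide refinements to it (Strengths and Limitations). Knowing which kinds of minor harm occurred, and how severe they were, bears on both.

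**Working it through.** The article gives no figure to reproduce on this point. The check is a comparison of the text, followed by an illustration under assumed rates.

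**1. The two rules side by side**

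| | Serious adverse events | Adverse events overall |
|---|---|---|
| Number of participants, by arm | not specified separately | yes |
| Number of events, by arm | yes (a number is planned) | not stated |
| Nature | yes | not stated |
| Severity | yes | not stated |

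No other section of the article adds type or severity for non-serious events. The second column counts everyone with any adverse event, including those whose event was serious, so it is not a count of non-serious harms alone.

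**2. What the all-cause count would show**

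Inputs from the article: "We will aim to enroll 48 participants" (Sample Size) and 1:1 allocation (Trial Design), hence 48/2 = 24 per arm. Dropout is ignored.

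Assumptions, because the article gives no rates: a proportion b of each arm has an unrelated adverse event; a proportion i of the exercise arm has a non-serious injury; controls have none; injury and unrelated events are independent.

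- Expected proportion with any event, exercise arm: 1 − (1 − b)(1 − i)
- Expected extra participants in the exercise arm: 24 × (1 − b) × i

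Worked case, b = 0.30 and i = 3/24 = 0.125:

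- Exercise arm: 1 − 0.70 × 0.875 = 0.3875, or 24 × 0.3875 = 9.3 participants.
- Control arm: 0.30, or 24 × 0.30 = 7.2 participants.
- Difference: 0.0875, about 9 percentage points. Standard error: √(0.30 × 0.70/24 + 0.3875 × 0.6125/24) = 0.137, about 14 points.
- Of the 3 injured, 3 × 0.30 = 0.9 on average would already be in the count because of an unrelated event.

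Range of assumptions:

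| Unrelated events b | i = 10% | i = 15% | i = 25% |
|---|---|---|---|
| 10% | 2.2 extra | 3.2 extra | 5.4 extra |
| 30% | 1.7 extra | 2.5 extra | 4.2 extra |
| 50% | 1.2 extra | 1.8 extra | 3.0 extra |

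At i = 10%, the chance that at least one of 24 exercisers is injured is 1 − 0.90^24 = 0.92. Some injury would therefore be likely, yet a bare participant count would not identify it as one.

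**3. Limits of the argument**

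- *Chance of no serious event.* At an assumed risk of 1% to 2% per participant, the exercise arm alone has none with probability 0.99^24 = 0.79 to 0.98^24 = 0.62. Over both arms, which is what the serious-event report covers, the figures are 0.99^48 = 0.62 to 0.98^48 = 0.38.
- *What a listing by type could prove.* Three injuries against none, 24 per arm, gives a two-sided Fisher p of 2 × C(24,3)/C(48,3) = 2 × 2,024/17,296 = 0.23. The listing would describe the injuries but would not establish an excess.

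**The case against.** **The sentences may be a minimum.** They say what will be reported and do not rule out more. An article condenses the full protocol, and event categories, grading and form fields are commonly left to that document. This stands in part. It disposes of any claim that relation to exercise is not recorded, or that the adverse event form lacks fields: both would be inferred from silence. It does not dispose of the main point. The article states a level of detail for each class of event, and the two levels differ.

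**The all-cause definition is sound.** It treats both arms alike. Participants and clinicians are unblinded, so judged relation to exercise is open to bias and hardly applies to controls. This stands. The wording "which does not necessarily have a causal relationship with the intervention" is no fault; the gap is that nature and severity are not planned for the events it captures.

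**Stronger readings.** A reader might infer that no exercise injury could appear in the results. That is not so: one leading to admission or lasting disability would be described. A reader might infer that the serious-event table will probably be empty. Over both arms that chance is 38% to 62% at the assumed risks, so the inference fails at 2% and is only modestly supported at 1%. A reader might infer that a real injury signal would be missed. With 24 per arm, three against none is itself inconclusive, so fuller reporting buys description, not proof.

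**Follow-up wording.** The reference to each follow-up time point is satisfied by the single visit 2 and needs no change.

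**Weight.** Safety is not among the stated objectives, which are cardiometabolic change and acceptability. That supports treating the point as minor.

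**Conclusion.** The point holds as a minor reporting weakness. As written, the article plans nature and severity for serious events only and a by-arm head count for adverse events overall. Non-serious exercise-type harms would not be distinguishable from unrelated illness in that report.

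The article gives no event rates, so the size can only be illustrated. Over unrelated-event rates of 10% to 50% and injury rates of 10% to 25%, injuries would add an expected 1.2 to 5.4 participants to the exercise arm's count of 24, unlabelled. These figures assume no injuries in controls, who also undergo CPET, and independence of injuries from other events. The conclusion about what the report would show follows from the text and does not depend on the rates.

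It rests on the article alone; a fuller plan in the full protocol or analysis plan would settle it. Nothing here touches the primary estimate, the significance level or the sample size.

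**What to change.** Extend the serious-event rule to all adverse events. Suggested replacement for the second reporting sentence:

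> For all adverse events, serious or not, the number of events and the number of participants affected will be given by study arm, by type (for example musculoskeletal, fall, cardiovascular or syncopal, other) and by severity. These tables are descriptive.

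Two secondary additions:

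- Where the data are recorded, note whether the event arose in a supervised session, a self-led session or CPET.
- If relation to exercise is judged, present it as supplementary, because the trial is open-label.

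If the full protocol already plans this, it is enough to align the published sentence with it.

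The cost is some extra coding and one more descriptive table, with small cells that should not be tested. By May 2025, 30 participants of the planned 48 had enrolled, so if session details were not collected from the start, that attribution would be partly retrospective and should be labelled so.
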